#### Clinician selection

Around 230 specialty clinicians (physicians and APPs) were identified who may see patients with the conditions selected for the trial, and therefore may be eligible to receive a nudge that their patient is eligible for genetic testing. Clinicians selected must 1) be currently in practice at Penn Medicine; and 2) have prescribing authority in Pennsylvania (physician or APP). Clinician clusters were formed to reduce confounding and randomized within clinical subspecialty (i.e. clinicians seeing patients within each of three disease groupings to be included in the trial: 1) pheochromocytoma/paraganglioma, 2) cardiology conditions, and 3) neurology conditions).

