#### Sample size, power, and statistical analysis

Based on preliminary data, up to 3800 patients are anticipated to be available to include in the study (based on prior assessment of eligible patients over the past three years), interacting with approximately 230 clinicians represented by approximately 100 clinician clusters. Clinician nudge assignment will be randomized by clinician cluster, while patient nudges will be assigned independently. This independent randomization makes the main effect for patient nudges a within-cluster comparison. The analysis will use the time to genetic testing outcome registered in the EHR within six months after the visit when the nudges were delivered. The exchangeable correlation (for our clustered data) observed from other studies is small (0.07). Our goal is to achieve at least 80% power using a two-sided type-1 error of 5%. Based on prior data, our outcome is expected to be 10% in the absence of intervention by the 6-month censoring time. We anticipate that the patient nudge will increase testing by 5% (HR=1.54), and clinician nudges will increase testing by 10% (HR=2.12). In addition, the two nudges together may increase testing more than the strict additive main effects and add up to an additional 10% testing (25% total increase). We calculated power by simulating random data sets in Stata 18. We assumed an exponential daily hazard with event times correlated within cluster and fitted those data sets with aCox regression model. Model variances were corrected using cluster-correlation. Our design yields more than 95% power for the patient and provider nudges regardless of correlation. It also provides at least 90% power to detect (within-between) interactions. Power remains above 80% for a wide variety of departures from our original assumptions. Power for the main effect of provider nudges may drop below 80% for high within-subject correlations (above 0.2), and overall power to detect all differences is reduced as the baseline hazard increases (beyond 20% testing by 6 months).

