Time to event outcomes (incidence of testing, incidence of ordering, incidence of referring, incidence of clinician action) will be analyzed using Cox regression, censoring at the six-month end of observation. The study design is factorial, and models will contain categorical predictor terms for clinician (refer vs. order vs. control) and/or patient nudge vs. control. We will include adjustments for fixed effects of site. We will control for type 1 error inflation by hierarchical testing, starting with the overall model significance, followed by overall effects of clinician nudges and then patient nudges. Once we have fitted the main effects model, we will test for interaction between clinician and patient nudges and retain that interaction term if significant (alpha=5%). We will test the two clinician nudges separately and combine them if there are no significant differences, and use a similar approach for other study outcomes using GLM (or GEE for repeated measures) using the appropriate distribution family.

While our design is factorial, with the presumption that a patient will remain in one clinician cluster, we recognize that there will be some movement or crossover between clinician clusters and treatments. For that reason, our primary analysis will censor patient observations at the point of crossover. We will also conduct a secondary analysis “as treated”, using time-varying covariates to represent the accumulated clinician nudge exposures over time.

Next, we will examine variability in our outcomes by treatment arm and moderators (patient-, clinician-, and system-level) using interaction terms within the regression. We will fit an adjusted model using the same approach described in the primary analysis. Moderators of particular interest will be patient-level (e.g., diagnosis, race, geocoded indicator of socio-economic status), clinician-level (e.g., years in practice), and system-level data (e.g., community vs. hospital-based). If there are no interactions with the two clinician nudge arms, they will be combined in subsequent moderator analysis following the same approach described above.

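### The clinician clusters were randomised within three disease groupings, but the stated model adjusts for site and does not name the grouping, so the clinician-nudge test may be needlessly conservative

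*Protocol article*

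**What the plan says.** **Randomisation.** Protocol article, *Clinician selection*, says the clusters were "randomized within clinical subspecialty (i.e. clinicians seeing patients within each of three disease groupings to be included in the trial". The groupings are pheochromocytoma/paraganglioma, cardiology conditions and neurology conditions.

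**Model.** *Sample size, power, and statistical analysis* says that "models will contain categorical predictor terms for clinician (refer vs. order vs. control) and/or patient nudge vs. control", and then: "We will include adjustments for fixed effects of site". Disease grouping is named neither as a covariate nor as a stratum. Diagnosis appears two paragraphs later in the list of moderators.

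**Variance.** The same section says that the time-to-event outcomes (testing, ordering, referring, clinician action) "will be analyzed using Cox regression, censoring at the six-month end of observation". For the rest, the team will "use a similar approach for other study outcomes using GLM (or GEE for repeated measures) using the appropriate distribution family". The one statement about clustered variance describes the power simulation: "Model variances were corrected using cluster-correlation".

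**The concern.** An analysis should normally condition on the factors used to restrict the randomisation. Allocation within grouping balances the arms on grouping, so differences between groupings add little to the true variability of the clinician-nudge estimate. A variance estimate from a model without grouping does not know this. It sees clusters with different testing rates and counts the whole spread as random error. The estimate stays usable, but its interval is too wide and its p-value too large.

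This bears on the contrast with the least information, because the clinician nudge is compared between about 100 clusters, whereas the patient nudge is compared within them. The testing hierarchy also places the clinician effect before the patient effect, so an over-conservative clinician test can hold up the next step.

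A smaller matter lies beside it. Correlation handling for the non-Cox outcomes is attached to repeated measurement, whereas the design feature that needs it is the randomised clinician cluster. An outcome recorded once per patient is still cluster-randomised for the clinician nudge.

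**Working it through.** **Inputs from the article:** up to 3,800 patients; about 100 clusters, so 3,800/100 = 38 per cluster; correlation 0.07; 10% tested at six months without nudges; patient nudge +5 points (HR 1.54); clinician nudge +10 points (HR 2.12); two-sided 5%.

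**Assumed:** equal clusters, 1:1:1 clinician allocation, 1:1 patient allocation, and the number of clusters and the testing rate in each grouping.

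**1. The plan's own figures.**
- HR = ln(1−p1)/ln(1−p0). Patient: ln(0.85)/ln(0.90) = 1.54. Clinician: ln(0.80)/ln(0.90) = 2.12. Both agree with the article.
- Design effect = 1 + 37 × 0.07 = 3.59.
- One nudge arm against control, averaging over the patient nudge (12.5% and 22.5% tested): events = (3,800/3) × (0.125 + 0.225) = 443, and 443/3.59 = 123.5 effective events. z = √(123.5 × 0.25) × ln 2.12 − 1.96 = 2.22, so power is 0.987.
- Both nudge arms against control: 728 events, 728/3.59 = 202.9. z = √(202.9 × 2/9) × ln 2.12 − 1.96 = 3.09, so power is 0.999.

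Both fit the stated figure of more than 95% at a correlation of 0.07, with no credit taken for stratification.

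**2. What omitting the grouping does.** Exponential event times were simulated for 100 clusters of 38 (10, 50 and 40 clusters per grouping), with latent within-cluster correlation 0.07 and cluster-robust variance. The contrast is either clinician nudge against none, on the log-hazard scale. There were 1,500 runs for type I error and 600 for power. Site was not modelled.

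| Six-month baseline by grouping | Without grouping: mean SE / true SD | Type I error | With grouping: mean SE / true SD | Type I error |
|---|---|---|---|---|
| 10/10/10% | 0.138 / 0.138 | 4.9% | 0.137 / 0.138 | 5.1% |
| 20/7/11% | 0.163 / 0.144 | 3.3% | 0.138 / 0.145 | 6.5% |
| 40/5/9% | 0.254 / 0.144 | 0.2% | 0.141 / 0.145 | 6.9% |

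The average baseline stays near 10% throughout: for example 0.1 × 20 + 0.5 × 7 + 0.4 × 11 = 9.9%.

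The true SD hardly changes when grouping is added. What changes is whether the reported SE matches it: 0.163/0.144 = 1.13 in the second row and 0.254/0.144 = 1.76 in the third. Power without grouping is about 100% in the second row and 92% in the third, and about 100% with grouping in both.

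**3. A rough analytic check.** Take three equal groupings at 5%, 10% and 20% (assumed). The mean is 0.1167 and the variance between them 0.00389. The ICC contribution is 0.00389/(0.1167 × 0.8833) = 0.038. If all of that lay inside the planned 0.07, the remainder would be 0.032, with design effect 1 + 37 × 0.032 = 2.2 and SE ratio √(2.2/3.59) = 0.78.

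**4. What ignoring clusters would do to a clinician contrast.** Type I error = 2 × [1 − Φ(1.96/√DEFF)]. With DEFF 3.59 it is 0.30. At ICC 0.03 (DEFF 2.11) it is 0.18, and at 0.01 (DEFF 1.37) it is 0.09. If 0.07 is a latent correlation, the simulation gives 15–18%. The patient nudge is a within-cluster comparison and is not inflated in this way.

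**The case against.** The strongest reply is that omitting the stratum errs on the safe side. The test is conservative, power at the planned correlation is 0.987 or more with no credit for strata, and even the extreme 40/5/9% case keeps 92% against a target of 80%. This stands, and it makes the point one of efficiency and coherence, not validity. Nor does the article say that site is the only adjustment. But site is the one it chose to name, and it is not the factor it randomised within.

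Adding the grouping is also not quite neutral in the simulation: type I error is 6.5–6.9%, with a simulation error of about 0.6 points (√(0.05 × 0.95/1,500)). The mean SE is then slightly below the true SD (0.138 against 0.145). That is a reason to look at the small-sample behaviour of the robust variance, not to leave the stratum out.

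Three stronger readings are tempting, and the document does not support them.

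- *The primary analysis has intervals that are too narrow.* The power simulation used cluster-corrected variance on Cox fits, so the planned Cox analysis most likely does too. The omitted stratum acts in the opposite direction.
- *Some planned tests have a 30% type I error.* Testing, ordering, referring and clinician action all go to Cox. The main named remainder is patient engagement with texts and video, and texts go out before the visit at which the clinician alert fires, so a clinician contrast there is not evidently planned. Changes to medical management are mentioned under *Duration* but are given no model. The phrase about a similar approach may also carry the cluster correction over, and an article may leave such detail to the analysis plan.
- *Adjustment would cut the standard error by 22%.* That follows from step 3, which assumes the rates and subtracts from a correlation observed in other studies. Nothing shows that the 0.07 contains variation between these groupings, and site adjustment may absorb some of it.

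**Conclusion.** The point holds in a limited form. The stated adjustment (site) is not the stated randomisation stratum (disease grouping). If testing rates differ between groupings, the reported clinician-nudge standard error is too wide and its test conservative. The excess ranges from nothing (equal rates) through about 13% (20/7/11%) to about 76% (40/5/9%). These figures rest on assumed rates, assumed numbers of clusters per grouping and equal cluster sizes, and they leave site out. The direction does not depend on the particular values, but the size does. The stated power need not change.

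The clustering remark is a clarification. The text ties GEE to repeated measures and does not say how a once-per-patient outcome would be handled in a clinician contrast, but no planned analysis is shown to be invalid.

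**What to change.** 1. State that the Cox models are stratified by disease grouping, or include it as a fixed effect, alongside site, and that the GLM and GEE models include it too.
2. State that every clinician-nudge contrast, including any on a once-per-patient outcome, uses variance clustered on the randomised clinician cluster, as the power simulation did. The analysis plan could also consider a small-sample correction, given the slight excess in type I error seen above.

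The cost is two sentences. The grouping is already known from the randomisation and, as a fixed effect, uses two degrees of freedom. Sample size and stated power can stay as they are. The change should be fixed before outcome data are compared by arm.

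### The stated power for the patient nudge, above 95% whatever the correlation, applies to a stand-alone test; in the planned testing order it is capped by the power for the clinician nudges

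*Protocol article*

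**What the plan says.** Everything is in the protocol article, section Sample size, power, and statistical analysis.

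- Power: "Our design yields more than 95% power for the patient and provider nudges regardless of correlation". The article adds that independent randomization of patient nudges makes their main effect a within-cluster comparison.
- A caveat shortly after: "Power for the main effect of provider nudges may drop below 80% for high within-subject correlations (above 0.2"). I read this as the within-cluster correlation.
- Multiplicity: error is to be controlled by "hierarchical testing, starting with the overall model significance, followed by overall effects of clinician nudges and then patient nudges".

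The power is said to come from simulated data sets fitted with a Cox model and cluster-corrected variances. The text does not say whether those simulations applied the testing order.

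**The concern.** The patient nudge is randomized by individual, so its own test hardly depends on clustering. The clinician nudge is randomized by cluster, so its test does. Placing the patient test behind the clinician test makes the patient claim inherit that dependence, and also makes it depend on the size of the clinician effect.

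At stake is one of the two factors of the trial. A real patient-nudge effect, detected on its own, could not be claimed if the clinician comparison missed for reasons unrelated to the patient nudge. The stated power gives no sign of this.

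**Working it through.** **Inputs from the section.** "up to 3800 patients are anticipated to be available to include in the study"; "interacting with approximately 230 clinicians represented by approximately 100 clinician clusters", so 3,800/100 = 38 patients per cluster; planning correlation 0.07; control rate 10% by six months; patient nudge +5 points (HR 1.54); clinician nudges +10 points (HR 2.12); two-sided 5%.

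**Assumed, because not stated.** Clusters 1:1:1 to order, refer and usual care; patients 1:1; equal clusters unless noted; the form of the within-cluster dependence.

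**Step 1, hazard ratios.** ln(0.85)/ln(0.90) = 1.54 and ln(0.80)/ln(0.90) = 2.12. Both match.

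**Step 2, stated power as stand-alone tests.** With additive rates, events = (3,800/6) × (0.10 + 0.15 + 2×0.20 + 2×0.25) = 728.3. Schoenfeld's formula gives z = ln(HR) × √(events × allocation product / design effect) − 1.96.

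- Clinician nudges pooled, correlation 0.07: design effect 1 + 37×0.07 = 3.59; z = 0.751 × √(728.3 × 1/3 × 2/3 / 3.59) − 1.96 = 3.08; power 99.9%.
- Correlation 0.20: design effect 8.4; power 91%. Correlation 0.30: design effect 12.1; power 78%.
- Patient nudge, no design effect: z = 0.432 × √(728.3/4) − 1.96 = 3.87; power above 99.9% if the HR of 1.54 holds in every clinician arm. With additive rates the HR within a nudged clinician arm is ln(0.75)/ln(0.80) = 1.29, and simulated stand-alone power is about 97%.

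So the figure of more than 95% is reproduced for both nudges at 0.07, and for the patient nudge tested alone at any correlation.

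**Step 3, the testing order.** P(patient claim) = P(clinician test rejects and patient test rejects), which is at most P(clinician test rejects). Simulation: rates 10/15/20/25%, exponential times, Gaussian copula, Cox model with cluster-robust variance, 2-df clinician test, 2,000 trials per row.

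| Correlation | Clinician | Patient alone | Patient through hierarchy |
|---|---|---|---|
| 0 | 100% | 97.3% | 97.3% |
| 0.07 | 99.6% | 97.1% | 96.6% |
| 0.15 | 94.4% | 97.3% | 91.7% |
| 0.20 | 88.8% | 97.2% | 86.4% |
| 0.25 | 81.5% | 96.9% | 78.9% |
| 0.30 | 74.8% | 97.0% | 72.4% |
| 0.40 | 60.7% | 97.3% | 58.8% |

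Check at 0.20: the joint probability must lie between 0.888 + 0.972 − 1 = 0.860 and 0.888; the simulation gives 0.864. The overall model test costs nothing visible (99.7% at 0.20). Smaller repeats of this scenario gave about 98% at 0.07, 86-87% at 0.20 and 72-73% at 0.30.

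**Step 4, dependence on the model.** Patient-nudge power through the hierarchy:

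| Scenario | 0.07 | 0.20 | 0.30 |
|---|---|---|---|
| Additive rates | 96.6% | 86.4% | 72.4% |
| Hazard ratios multiply | 100% | 95.0% | 85.3% |
| 35% tested with both nudges | 100% | 99.2% | 95.7% |
| Additive, unequal clusters (CV 0.8, assumed) | 95.4% | 73.9% | 58.9% |
| HRs 1.54 and 2.12, correlation read as ICC of the six-month yes/no outcome | 98.9% | 79.2% | 59.5% (repeat 65.5%) |

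In the last scenario, pooling the clinician nudges into a 1-df gate gives 86% at 0.20 and 72% at 0.30. A Clayton copula (Kendall tau 0.30, additive rates) gives 84.0%. The scale matters: at a 10% event rate a latent correlation of 0.20 is a yes/no ICC of only 0.080.

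**Step 5, a weaker clinician effect at 0.07.** If the clinician nudge adds 5 points, power through the hierarchy is 64-69%, against 98-99% stand-alone. If it adds nothing, 6-7% against 99% or more; the gate then opens at roughly its own type 1 error rate.

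**Step 6, Holm over the 2-df clinician test and the patient test.** Patient power is about 95% to 100% across the scenarios tried. Clinician power changes by at most about 0.7 points where the patient effect is real, and falls from 98% to 96% at 0.07 if the patient nudge has no effect.

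**The case against.** A fixed sequence is valid, and putting the larger assumed effect first is ordinary practice. At 0.07 with additive rates the clinician test is in fact the stronger one (99.6% against 97.1%). The article gives an order but does not spell out what happens after a failed step; an analysis plan may do so. The section already warns about provider-nudge power above 0.2.

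Most of this stands. The order is a legitimate choice, and the gate is my reading. It is the natural one, because an order without a gate would not control type 1 error as the article says it does. What does not stand is the power sentence: no rule that makes the order do its work leaves patient-nudge power free of the correlation. For the provider nudges, the sentence also conflicts with the section's own caveat.

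A reader might infer two stronger things. One is that the patient comparison is underpowered as planned. It is not: at 0.07 and the assumed effects, every scenario gives 95.4% or more, against a goal of 80%. The other is that patient-nudge power drops below 80% once the correlation passes 0.2. The document does not fix the correlation scale or the effect model well enough to say so. With additive rates the crossing is near 0.25, and in some scenarios power is still above 80% at 0.30.

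**Conclusion.** The point holds as a mismatch between the stated power and the planned testing rule. The cap itself is logical and needs no simulation, given that the hierarchy is a gate. Its size depends on departures from the planning assumptions:

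- At 0.07 and the assumed effects, the loss is about 1 point or less with equal clusters and 97.2 − 95.4 = 1.8 points with the assumed unequal clusters.
- At higher correlation, power is about 79-99% at 0.20 and 60-96% at 0.30 with equal clusters; unequal clusters lower the bottom of these ranges to 74% and 59%.
- The largest exposure is a clinician effect smaller than assumed, which can occur at the planned correlation.

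Allocation ratios, dependence model and cluster-size spread are my assumptions, so these are ranges and not corrected values for the plan.

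**What to change.** Preferably before outcome data are seen, do one of the following.

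1. Keep the order and correct the power text. Limit the statement about correlation to the patient nudge tested alone, drop it for the provider nudges, and report patient-nudge power through the hierarchy over a range of correlations and clinician effects, naming the correlation scale. State that a patient-nudge claim requires a significant clinician test. The cost is a less favourable stated power.
2. Replace the clinician-then-patient order with Holm's procedure over the 2-df clinician test and the patient test at an overall 5%, and say whether the overall model test stays as a first step. This makes the stated patient-nudge power essentially true. The cost is one sentence, plus about 2 points of clinician-nudge power at 0.07 if the patient nudge has no effect.

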## Methods

### Study design

The study will test optimized implementation strategies informed by behavioral economics in a six-arm factorial hybrid type 3 cluster implementation RCT testing the effectiveness of nudges to clinicians (to either refer to a genetics clinic or order genetic testing), nudges to patients (to discuss genetic testing with their clinician), nudges to both, or neither (Fig. 2). The two versions of the clinician nudge will help to test the effects of a local adaptation to this implementation strategy.

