**Fig. 4 Fig4:**
[figure not shown]
PennChart Genomics Initiative website. Publicly available link: https://www.med.upenn.edu/pgi/

Moderators of effectiveness will be investigated through analyzing associations with variables available via EHR for patients (e.g., race) and clinicians (e.g., location of practice). Tracking referrals and genetic test orders in the EHR will allow for comparisons in uptake across clinics and patient groups.

The primary implementation outcome will be the time to genetic testing within six months of the patient’s initial visit with a randomized clinician. Each of the six randomization groups, as detailed in Fig. 2, will be analyzed separately.

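### Keeping the clinician-by-patient interaction only if p<0.05 lets a low-powered test decide what the patient-nudge hazard ratio means, and biases single-nudge effects read from the reduced model

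*Protocol article*

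**What the plan says.** The Study design section sets up a six-arm factorial trial of clinician nudges (refer or order), "nudges to patients (to discuss genetic testing with their clinician), nudges to both, or neither". At the end of that section, after the Fig. 4 caption, it adds: "Each of the six randomization groups, as detailed in Fig. 2, will be analyzed separately".

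The only primary model is in Sample size, power, and statistical analysis. It is a Cox model with categorical terms for the clinician nudge (three levels) and the patient nudge. Testing is hierarchical: overall model, then clinician nudges, then patient nudges. After the main-effects fit, "we will test for interaction between clinician and patient nudges and retain that interaction term if significant (alpha=5"%).

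The same section assumes 10% testing by six months with no nudge, 15% with the patient nudge (HR 1.54) and 20% with a clinician nudge (HR 2.12). For the combination it says "the two nudges together may increase testing more than the strict additive main effects and add up to an additional 10% testing", which is at most 35%. It claims at least 90% power for interactions.

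**The concern.** If the interaction is not significant, the main-effects model stands. That model forces the patient-nudge HR to be the same with and without a clinician nudge, and forces both versus neither to equal the product of the two main effects. If the interaction is significant, the patient-nudge coefficient becomes a different quantity: the effect among patients whose clinicians receive no nudge. The estimand thus depends on a p-value, and non-significance is in effect read as absence of interaction.

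The trial asks about patient nudges, clinician nudges, both or neither. Whether texting patients works without a clinician alert is a simple effect (the effect of one nudge when the other is absent), and the reduced model does not estimate it. A reader who trusts the stated interaction power would take a dropped term as good evidence that the nudges act independently.

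**Working it through.** **Inputs from the protocol article.** Six-month testing of 10, 15, 20 and up to 35%; "up to 3800 patients are anticipated to be available to include in the study"; "approximately 230 clinicians represented by approximately 100 clinician clusters"; a two-sided alpha of 0.05 with a power target of 80%; and, on clustering, "The exchangeable correlation (for our clustered data) observed from other studies is small (0.07"). **Assumed:** equal allocation to six arms (633.3 patients each), equal cluster sizes, equal refer and order effects, no crossover censoring and no site adjustment.

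**1. Reproduce the plan's HRs.** HR = ln(1-p)/ln(1-p0).
- Patient: ln(0.85)/ln(0.90) = 1.54, as stated.
- Clinician: ln(0.80)/ln(0.90) = 2.12, as stated.
- Both at 35%: ln(0.65)/ln(0.90) = 4.09.

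**2. Interaction on the Cox scale.** No interaction would give 1.54 x 2.12 = 3.27. The interaction HR is 4.09/3.27 = 1.25 (log 0.224).

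**3. Power of the interaction test.** Expected events are 63.3 (neither), 95 (patient), 253.3 (clinician, refer and order pooled) and 443.3 (both).
- SE = sqrt(1/63.3 + 1/95 + 1/253.3 + 1/443.3) = 0.180.
- z = 0.224/0.180 = 1.24, so two-sided power is about 24%.
- With refer and order kept apart (2 df) it is 18%. With four equal cells, the most favourable layout tried, it is 29%.
- Simulation gives 23-25%, 20-21% and 31% respectively.

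The stated 90% is not reproduced on the Cox scale. It would need an interaction HR of about exp(3.24 x 0.180) = 1.79. It is reached only on the risk-difference scale (97.5% with clinician arms pooled, 89.9% with one clinician arm).

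**4. What the reduced model estimates.** The common patient-nudge log HR is roughly an information-weighted mean of two simple effects.
- Without a clinician nudge: log 1.54 = 0.433, information 63.3 x 95/158.3 = 38.0.
- With a clinician nudge: log(4.09/2.12) = 0.658, information 253.3 x 443.3/696.7 = 161.2.
- Weighted: (38.0 x 0.433 + 161.2 x 0.658)/199.2 = 0.615, so HR = 1.85.

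The reduced model therefore reports mostly the effect in the presence of a clinician nudge.

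**5. Coverage under the rule.** Simulation used 3,800 patients, 100 clusters, exponential times, within-cluster correlation 0.07 (Gaussian copula) and Cox models with cluster-robust variance. The true patient-alone HR is 1.54 and the true clinician-alone HR is 2.12 in every row.

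| Tested with both nudges | Patient HR when term dropped | Patient alone under the rule: mean HR, coverage | Clinician alone, coverage | Both vs neither, coverage |
|---|---|---|---|---|
| 35% (plan's ceiling) | 1.85 | 1.71, 41.9% | 79.5% | 88.9% |
| 30% | 1.60 | 1.58, 89.9% | 92.5% | 93.5% |
| 25% (strictly additive) | 1.35 | 1.43, 61.3% | 86.7% | 92.5% |

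With the interaction always kept, coverage of all three effects is 94.4-94.8% in every row.

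At 35%, with the 2-df pretest, patient-alone coverage is 39%; with four equal cells it is 61%. Both versus neither ranges over 87-91% across variants, with a mean HR of 4.37 against 4.09. For correlations from 0 to 0.2, clinician-alone coverage runs from 70 to 86%.

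A separate simulation with gamma frailty (variance 0.07) gives 43% patient-alone coverage at 35% and 59% at 25%. There the patient coefficient at 35% averages 1.85 when the term is dropped and 1.29 when it is kept, so the two branches err in opposite directions.

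**The case against.** **The main-effect tests are sound.** The overall clinician and patient tests come before the interaction step, so their type I error is unaffected. A reader might infer that the primary tests are invalid; the document does not support that. The low coverage arises only when the reduced-model coefficient is read as a simple effect, and the article never says it will be labelled patient nudge alone. This stands and limits the point. But the article sets out to compare the nudges singly and together and gives no other model for doing so.

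**A significant patient effect is not a false positive when the nudge works only alongside a clinician nudge.** Take an illustrative 10/10/20/25%, which is not a plan scenario. The averaged effect is real: information 31.7 and 140.7, log HRs 0 and 0.254, weighted mean 0.207, HR 1.23. Rejecting no average effect is correct, and the fix keeps that test (z = 0.207 x sqrt(172.4) = 2.72, power about 78% ignoring clustering). The risk is mislabelling, not a wrong test.

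**Both versus neither.** A reader might infer that this interval fails as badly as the patient-alone one. It does not: coverage is about 87-91% and the HR bias about 7%.

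**35% is a ceiling.** At 30% the HR is 3.39 against a product of 3.27, and the harm is small. The bias depends on the truth, which is not known in advance.

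**Separate analysis of six groups.** Arm-level comparisons would avoid the bias. But a model with the interaction dropped does not analyse six groups separately, so the two statements conflict, and the first does not cure the second.

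**Conclusion.** The concern holds in limited form. The retain-if-significant rule makes the meaning of the patient-nudge HR depend on a test with about 20-30% power at the plan's largest assumed synergy. When the term is dropped, patient nudge alone reads about 1.85 instead of 1.54, and under the rule its interval covers about 40% of the time. Clinician alone covers about 80%; both versus neither is mildly low. With strictly additive effects the bias reverses (patient-alone coverage about 60%), and at 30% it is small (about 88-90%).

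The hierarchical main-effect tests are not invalidated. Correcting the interaction power figure alone would not remove the problem, because the drop rule would remain. The sizes rest on the allocation, cluster-size and equal-effect assumptions listed with the inputs. The direction and rough size were the same under two different models for within-cluster correlation.

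**What to change.** Replace the retain-if-significant sentence in Sample size, power, and statistical analysis with wording to this effect:

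- The hierarchical clinician and patient tests come from the main-effects model and are reported as effects averaged over the other factor, whatever the interaction result.
- The model with the clinician-by-patient interaction is always fitted as well. From it are reported the HR and 95% CI for patient nudge alone, each clinician nudge alone and each combination versus neither, and the interaction HR with its CI.
- Absence of interaction is not inferred from p>0.05.

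This also reconciles the analysis section with the separate analysis of six groups promised under Study design.

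Cost: a few sentences and one more model fit, with no added patients or data. The price is precision. For patient nudge alone the SE of the log HR is about 1/sqrt(38.0) = 0.162, against 1/sqrt(199.2) = 0.071 for the averaged effect, so the interval is about 2.3 times as wide. Power for patient nudge alone is about 75% in the plan's scenario, against nearly 100% for the averaged effect. The main-effect tests and their power do not change.
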